**Figure 2. f2:**
[figure not shown]
Study design and flow for the three scale-up cities and the three comparator cities, with data gathered during each measurement period. PHCU, primary health care unit.

### Cities

Intervention municipalities that have confirmed technical and political consent to be involved have been investigator-selected from Bogotá (Colombia), Mexico City (Mexico) and Lima (Peru). Comparator municipalities have been investigator-selected in Bogotá, Mexico City and Lima, on the basis of comparability with the scale-up municipality in terms of socio-economic and other characteristics which impact on drinking, health care and survival, comparable community mental health services, and sufficient geographical separation to minimize spillover effects from the intervention municipality. Randomized selection of the municipalities was excluded as the hypotheses and the study approach relies on municipal-level interventions. Cities are chosen as the scalable unit, as there is a systemic global trend for municipalities to increasingly take on the jurisdictional responsibilities for prevention and health care services. Cities, themselves, are active in prevention and health promotion programmes, and there is a strong evidence base for their impact, also in the prevention of alcohol-related harm
^85,
86^. Cities are a natural site for preventing alcohol-related harm
^87^. Although not having the full jurisdictional responsibilities of national governments for all alcohol policy issues, they often have greater flexibility and are an important site for both media-based and social norms programmes, as well as environmental measures to manage and limit availability of alcohol
^88^. Networks of cities are natural vehicles for exploitation of the results and deployment to full scale, more so with the trends of increasing urbanization in Latin America
^89,
90^.

### Primary health care

Primary care-focused health initiatives can improve access to health care, including among the poor, at reasonably low cost in low- and middle-income countries
^91^, and particularly so in Latin America
^90^. Health-system reforms in Latin America have placed a strong emphasis on the development of comprehensive PHC as a vehicle to achieve universal health coverage, reduce inequities, and democratise health through participation. However, they face ongoing challenges, in particular, the development of health services that can meet the emerging health needs brought on by social and demographic transitions, including the increasing chronic disease burden, and the impacts of rapid urbanisation
^92^.

Management of chronic diseases relies on opportunistic case finding, assessment of risk factors, detection of early disease, identification of high-risk status, combined psychosocial and pharmacological interventions, and long-term follow-up with regular monitoring and promotion of adherence to advice and treatment. Such approaches are financially feasible and have the potential to substantially reduce the burden of chronic diseases. Many interventions can be managed effectively by non-specialists and lay health care workers who are supported by specialists. Although implemented in a range of settings, collaborative care models seem best delivered in PHC settings
^93^. Evidence demonstrates the effectiveness of PHC-based lifestyle interventions in Latin American contexts
^94,
95^, including brief advice programmes to reduce heavy drinking, as well as the potential to detect and refer high-risk patients.

### Participants

Approximately ten PHCUs per intervention and comparator cities will be involved, 60 PHCUs in total. The exact number of PHCUs will depend on the average number of registered patients per PHCU. In each city, the total number of recruited PHCUs should cover a population of about 80,000 registered patients (including children and adults). In jurisdictions, where PHC physicians work as individual practitioners, a PHCU can be defined for the purposes of the study as a virtual or physical location where three or more PHC physicians work. Identification of PHCUs who agree to participate in the studies will be drawn from administrative or academic registries of PHCUs at national, regional, or city levels. The process of recruiting PHCU will be described in detail by each country. Within each PHCU, eligible providers will include any fully trained medical practitioner, nurse or practice assistant with a non-temporary employment contract, working in the PHCU and involved in medical and/or preventive care. These providers will sign an informed consent for their participation. Dependent on customary country practice, participating PHCUs will receive a study fee.

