### Sample size

Our power calculations are based on the following assumptions: at baseline, 2.5/1,000 consulting patients will be found to be screen positive (based on an AUDIT-C cut-off score of 8) and advised to reduce their alcohol consumption (data from ODHIN study; [name], personal communication). To detect an increase in the number to 5/1,000 (a doubling), with 80% power and a significance level of 5%, and assuming a design effect of ten PHCUs per three cities per group (scale-up and comparator), with an ICC for PHCUs across countries = 0.03 (data from ODHIN study; [name], personal communication), a conservative estimate of 30 PHCUs across three scale-up cities and 30 across three comparator cities, about ten per city will be needed
^150^, assuming an average PHCU size of about 8,000 patients with a monthly consultation rate of 1,200 adult patients per PHCU (data from ODHIN study; [name], personal communication).

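### The recruitment rule sets no minimum number of primary health care units, although the sample-size requirement is a count of units

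*Protocol article*

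**What the plan says.** The Participants section of the protocol article gives two targets. The first is a count: roughly ten PHCUs in each intervention and comparator city, 60 overall. The second is a population: in each city "the total number of recruited PHCUs should cover a population of about 80,000 registered patients", children included. The sentence between them says which one gives way: "The exact number of PHCUs will depend on the average number of registered patients per PHCU". The section states neither a minimum number of PHCUs nor an upper limit on PHCU size.

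The Sample size section states the requirement as a count: "a conservative estimate of 30 PHCUs across three scale-up cities and 30 across three comparator cities", about ten per city. It rests on a doubling from 2.5 to 5 per 1,000 with 80% power at the 5% level, "with an ICC for PHCUs across countries = 0.03", and "assuming an average PHCU size of about 8,000 patients with a monthly consultation rate of 1,200 adult patients per PHCU".

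**The concern.** The two sections coincide at one point only: ten PHCUs of 8,000 patients make 80,000. Away from that average, the Participants section lets the count move to hold the population. A city with five PHCUs of 16,000 patients would reach 80,000 with half the number that the Sample size section calls for.

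When outcomes within a PHCU are correlated, further consultations in the same PHCU soon add little, while each further PHCU adds nearly its full share. The rule therefore holds fixed the quantity that matters less and lets the more important one vary. Recruitment could be reported as complete with fewer clusters than planned, and the confidence interval for the intervention effect would be correspondingly wider.

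**Working it through.** **Inputs** (Sample size and Participants sections): p1 = 0.0025, p2 = 0.005, 80% power, alpha 5% (sidedness not stated; two-sided assumed), ICC = 0.03, 8,000 registered patients and 1,200 adult consultations a month per PHCU, three cities per group, 80,000 registered patients per city.

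**1. The plan's own figure.** Comparing two proportions with pooled variance under the null:

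n = [1.96 × √(2 × 0.00375 × 0.99625) + 0.8416 × √(0.0025 × 0.9975 + 0.005 × 0.995)]² / 0.0025² = 9,383 per group.

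Design effect = 1 + (1,200 − 1) × 0.03 = 36.97.

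PHCUs per group = 9,383 × 36.97 / 1,200 = 289.1, so about 290. The stated 30 is not reproduced; one-sided, continuity-corrected, unpooled and arcsine variants give 228 to 313. Power with 30 PHCUs of 1,200 consultations is 14.5% (23% one-sided). Pooling two four-week periods (2,400 per PHCU) gives 14.6%.

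**2. Holding the population and varying PHCU size.** Registered patients per group: 3 × 80,000 = 240,000. Consultations per group and month: 240,000 × 1,200 / 8,000 = 36,000, assuming that consultations scale with registered patients. For average size S, the number of PHCUs is k = 240,000/S and consultations per PHCU are m = 36,000/k. Effective n = 36,000 / [1 + (m − 1) × 0.03].

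| Average size | PHCUs per group | m | Design effect | Effective n per group | Power |
|---|---|---|---|---|---|
| 4,000 | 60 | 600 | 18.97 | 1,898 | 24% |
| 8,000 | 30 | 1,200 | 36.97 | 974 | 14.5% |
| 12,000 | 20 | 1,800 | 54.97 | 655 | 11% |
| 16,000 | 15 | 2,400 | 72.97 | 493 | 9% |

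Relative to 974, effective n is 33% lower at 655 and 49% lower at 493.

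**3. Holding the number and varying PHCU size.** With 30 PHCUs per group, effective n cannot exceed about 30/0.03 = 1,000. It is 903 at m = 300 (power 13.8%) and 993 at m = 4,800 (14.7%). A sixteen-fold change in consultations per PHCU moves power by about one percentage point.

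**4. Illustration with an ICC that is not in the document.** For 30 PHCUs of 1,200 to give exactly 80%, the design effect would have to be 36,000 / 9,383 = 3.84, so ICC = (3.84 − 1) / 1,199 = 0.0024. At that ICC, power is 67% with 20 PHCUs and 57% with 15.

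**5. Sensitivity to the ICC** (assumed values; 30, then 20, then 15 PHCUs per group):
- 0.001: 96%, 91%, 85%
- 0.005: 55%, 41%, 33%
- 0.01: 33%, 24%, 19%

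**The case against.** The number is not left open. The Participants section begins with about ten PHCUs per city and 60 in total, both targets are approximate, and at the assumed average size they match. The fair reading is a planned ten with some flexibility. This stands. It would be too strong to say that population replaces the count as a declared binding rule. What remains is that, when the two diverge, the text lets the count move and gives no floor.

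The rule also works in both directions, and nothing in the article indicates PHCUs of 12,000 or 16,000. This stands too: those sizes are hypothetical, and PHCUs of 4,000 would raise power. A floor costs nothing where PHCUs are small.

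A reader might infer that the recruitment rule pulls power from 80% down to 67% or 57%. The document does not support that. Those figures need the back-solved ICC of 0.0024. At the stated 0.03, power with exactly 30 PHCUs is already about 14.5%, and the rule lowers it further to 11% or 9%.

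A reader might also infer that precision would differ between intervention and comparator groups. The article gives no PHCU sizes by municipality and says that comparators were chosen for comparability, so there is no basis for a figure.

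Finally, the article leaves the detail of PHCU recruitment to each country, and a floor could be written there. But the text deferred is about the process; the article itself states how the number is set.

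**Conclusion.** The point holds as a gap between two sections. The sample-size requirement is a number of PHCUs, and the recruitment text lets that number fall if PHCUs are larger than about 8,000 patients, without a minimum. At the stated ICC, halving the number of PHCUs at constant population roughly halves effective sample size (974 to 493 per group), with power going from about 14.5% to 9%. These figures assume two-sided testing, consultations proportional to registered patients, one four-week period, equal PHCU sizes, and no allowance for city-level variation or baseline adjustment. The direction does not depend on the exact ICC. The loss is modest only at an ICC far below the stated one, such as 0.001.

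This is secondary to the error in the Sample size section, where 30 PHCUs per group do not give 80% power at the stated inputs. A floor of 30 would protect the planned precision but would not restore the claimed power.

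**What to change.** In the Participants section, state the number of PHCUs as a minimum and call the 80,000 registered patients per city indicative. The minimum should be the ten per city (30 per group) already planned, or the number that results once the Sample size section is recalculated; the recalculation should come first.

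This is a change of wording. In cities with large PHCUs, more units would have to be recruited and, in intervention cities, trained than the population target alone would require, but no more than the 60 already planned if the floor stays at ten per city. A higher floor after recalculation would cost more, and that cost belongs to correcting the sample size. Recording by only some providers in large PHCUs could limit the workload, but it is optional: it would have to be squared with the care pathway, under which every visiting adult is screened.

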### SCALA care pathway for heavy drinking

The SCALA care pathway includes three integrated components:
i. preventing the development of heavy drinking via increased alcohol health literacy;ii. screening and brief advice to reduce the prevalence of heavy drinking; andiii. diagnosis and clinical management of severe AUD and/or co-morbid depression.

The SCALA intervention package deals primarily with the first two parts, prevention and management of heavy drinking. It does not specifically address managing severe AUD, including alcohol-related physical complications and/or severe co-morbid mental health conditions, but ensures the necessary links with specialist services in order to do so, even though specialist treatment can be managed in PHC, with appropriate support
^67,
96^.

Whilst AUDIT-C is highly effective at identifying heavy drinking, it is not designed to stratify patients by severity of AUD, nor designed to diagnose depression, commonly comorbid with heavy drinking. A DSM-5 11-item instrument can be used to stratify the severity of AUD into mild (2–3 items), moderate (4–5 items) and severe (6+ items)
^97^. Similarly, the Patient Health Questionnaire 9 (PHQ-9), can be used to diagnose moderately severe or severe depression with a cut-off score of 15+
^98^. In our protocol, patients scoring 8+ on AUDIT-C, will be further screened with the DSM-5 11-item instrument and the PHQ-9 to assess severity of AUD and to identify patients with co-morbid depression.

For the care pathway (
Figure 3), all adult patients (age 18+ years) visiting the PHCU for whatever reason will be screened with AUDIT-C, with country-specific pictograms of standard alcohol beverages used to identify the standard unit (drink) of alcohol. Patients with an AUDIT-C score of <8 will be given a patient information leaflet to improve alcohol health literacy (knowledge of the risks of drinking alcohol, and skills to achieve and maintain lower risk drinking, defined as no more than 20g of alcohol per day). Patients with an AUDIT-C score of 8+ will be invited to complete the DSM-5 11-item instrument and the PHQ-9: those with an 11-item score of <6 and a PHQ-9 score of < 15 will be given brief advice of between 5–10 minutes, based on the FRAMES principles
^99^. Those with an 11-item score of 6+ and/or a PHQ-9 score of 15+ will be refereed to more specialist services, at the clinical decision of the health care provider A record of what steps are taken will be recorded on paper or electronic tally sheets prepared for the study.

**Figure 3. f3:**
[figure not shown]
Comprehensive care pathway of SCALA. For screen negative patients, screen positive patients without AUD and depression and for screen positive patients with AUD and/or depression. PHCU, primary health care unit; AUD, alcohol use disorder.

### Implementation strategies

In the intervention cities, implementation strategies will comprise three components: tailoring the PHC screening and advice package; providing specific practice-based training and ongoing support to PHCUs; and, implementing city-based adoption mechanisms and support systems, including media-based campaigns to improve alcohol health literacy. In the intervention cities, all PHCUs will be given a summary card of screening and advice procedures, with instruction, instruction on how to complete record sheets, and record sheets. In the control cities, all PHCUs will be given a summary card of screening and advice protocol, with no instruction, instruction on how to complete record sheets, and record sheets. As part of the study, no other action will take place in the control cities.

### Tailoring PHC screening and advice package

SCALA is a trans-cultural study, with different health systems, and differences in drinking patterns and attendance at PHC centres, compounded by gender differences. In Mexico, for example, men consume more alcohol then women, but attend PHC services much less frequently than women
^53^. Thus, there is a need for careful tailoring of the screening and advice package. Each intervention city will create Community Advisory Boards (CABs) representing academia, city health and public health departments, health service commissioners and practitioners, and patient and public engagement groups; and User Panels (UPs) of user groups, including PHC providers, patients and citizens. Through expert meetings, workshops, and focus groups, the package will be fine-tuned and tailored to the needs of each city, based on the Tailored Implementation for Chronic Diseases initiative
^100–
102^ within the seven domains of: local and national guideline factors; individual health care provider factors; patient factors; interactions between different professional groups; incentives and resources; capacity for organizational change; and, social, political and legal factors. At the city level, tailoring will be based on the principles of integration between PHC and municipal services
^103^ and the development of complementary community ecosystems that support reductions in heavy drinking. At the PHC level, tailoring will be based on the principles of co-production of health
^104^ between PHC providers and patients.

### Training and ongoing support of PHCUs

In the intervention cities, PHCUs will be offered two initial two-hour face-to-face educational trainings prior to the 18-month scale-up phase, and two one-hour booster sessions during the first twelve months of the 18-month scale-up phase. Training will take place within the PHCU or clusters of PHCUs. Training will be undertaken by peer trainers, members of the research team, accredited teachers, or addiction consultants. Training will focus on management and administrative skills within the primary health care center, on practical skills in undertaking screening and in delivering brief advice, in using the questionnaires, and in knowing when and how to refer patients with more severe AUD
^105–
108^ and moderately severe or severe depression to available services, such as community-based mental health and addiction centers
^67^. Training will, in addition, address attitudes, and perceived barriers and facilitators
^109–
111^ in implementing screening and brief advice, contextualized to local circumstances
^112^. Each country will use an adapted existing country-based training and support package. Where these do not exist, training and support packages will be adapted based on the PHEPA (Primary Health Care European Project on Alcohol) training programme
^113^, widely implemented since 2002 in Catalonia, a Catalan/Spanish speaking, bilingual geographic area. The PHEPA training programme is similar to those used in the WHO Phase III trial
^45^ and the ODHIN study
^41^.

### Implementing city-based adoption mechanisms and support systems

Within each intervention city, an integrator (champion and knowledge and practice broker) will be appointed with responsibilities of serving as a trusted and accountable leader: facilitating agreement within the city and health systems on shared goals and metrics; assessing and acting on relevant community resources; working at the systems level to make relevant practice changes for sustainability; gathering, analyzing, monitoring, integrating, learning, and sharing data at the individual PHCU and city levels; identifying and connecting with system navigators who help PHCUs coordinate, access, and manage multiple services and supports; and developing a system of ongoing and intentional communication with PHCUs and cities.

Within each intervention municipality, the Community Advisory Boards will identify adoption mechanisms that can be used for scale-up, for example: (i) demonstration of the superiority of the PHC package, its simplicity, and its alignment with the latest evidence of preventing and managing heavy drinking and of implementation science; (ii) engagement of identified leaders and building their capacity to lead and ensure broad adoption of the PHC package through guiding and supporting large-scale change
^114–
116^; (iii) communicating the value of the PHC package to both municipal and PHC frontline staff
^117^; (iv) identifying and adjusting, as appropriate and possible, relevant policies at PHC and city levels to expedite the adoption of the PHC package, for example by adapting electronic health records; and, (v) identifying gaps in health system performance and the urgent need to prevent and manage heavy drinking to promote the needed will and energy to bring implementation of the PHC package to scale
^118^.

The Community Advisory Boards will also identify additional mechanisms that can be used to support scale-up, for example: (i) development of professional capacity for scale-up; (ii) development of infrastructure for scale-up, achieved through redesign rather than addition of new resources; (iii) linking to monitoring and evaluation, using reliable data collection and reporting systems that track and provide feedback on the performance of key processes and outcomes, for example monthly reporting on screening and brief advice activity; (iv) setting up learning systems to capture change ideas that are shown to result in improved performance assembling ideas into a change package. Knowledge should be shared between municipal actors and PHCUs through regular electronic newsletters and communications
^119^; and, (v) creating design factors that enhance sustainability including high reliability of the new processes, inspection systems to ensure desired results are being achieved, support for structural elements, and ongoing learning systems
^120,
121^.

### Data collection

Based on the validated methodology of the ODHIN project
^41,
122^, PHC providers will document activity by completing paper or electronic (depending on the ability to use existing electronic health records) anonymous tally sheets that record eligible patients’ (aged 18+ years) AUDIT-C scores, if administered, DSM-5 11-item and PHQ-9 scores, and the advice or treatment given to each patient. The tally sheets will record the age, sex, employment status, and educational level of the patient, the latter as one proxy measure of socio-economic status. The tally sheets will also include: two questions that capture previous experience of being asked about how much the patient drinks and of being advised to reduce the amount drunk to provide information for UN Sustainable Development Goal 3.5
^12^; one question about alcohol being a cause of high blood pressure, liver problems, depression or cancer, as a simple measure of alcohol health literacy (knowledge part)
^123^; and, two questions about injunctive social norms of drinking alcohol
^124^.

Data will be collected for each calendar month during the 18-month scale-up period. Formal evaluation will take place during three measurement periods: 4-week baseline period; 4-week assessment period during the 9
^th^ month of the 18-month scale-up period; and, 4-week assessment period at 18-months, the end of scale-up period. PHCUs will return data on the number of adult (aged 18+ years) consultations per provider for the four-week baseline assessment period, and for each of the 18 months of the scale-up period.

At baseline, PHC providers will provide data on their age, sex and profession (doctor, nurse, practice assistant etc.). At baseline, and at two time points during the 18-month scale-up period (month 4.5 and month 13.5), providers will provide data on their alcohol health literacy and on their attitudes to working with patients with heavy drinking. The alcohol health literacy instrument will assess knowledge of risks due to drinking
^123^, and descriptive and injunctive social norms
^124^. The attitudes instrument will be the shortened version of the Alcohol and Alcohol Problems Perception questionnaire
^125^.

During month 3 of the 18-month implementation period, the first six consecutive screen positive patients identified by each PHC provider will be invited to give their consent to complete two follow-up questionnaires, at six months and twelve months after the initial screening. The patient interviews will be used for quality control
^126^, but not as a study outcome measure. The follow-up questionnaires will be the same as the baseline questionnaire and will be undertaken by the local academic unit by face-to-face or telephone interview. Collected data will include sex, age, educational level, alcohol consumption (operationalized by AUDIT-C), alcohol health literacy, prevalence of depressive symptoms using the nine-item patient health questionnaire
^98^, experience of screening and brief advice and treatment for heavy drinking, experience of self- and co-management for heavy drinking and health service utilization.

Process evaluation will be ongoing through interviews with CABs, with formal evaluation time points at baseline, ninth month of the 18-month scale-up period, and at the end of the scale-up period. Logic models will be developed and data will be collected on drivers, facilitators and barriers of successful implementation
^127,
128^. City and country-based contextual, financial and political-economy factors will be collected (see outcomes below).

During all phases of the scale-up, we will document impact on other sectors (education, social care, criminal and justice, etc.) based on resource use measurement
^129^. Patients in the scale-up and comparator cities will be asked to complete a short questionnaire about resource use measurement. Costs will be calculated by multiplying volumes (resource use) with unit costs, based on guideline prices
^130^. Health and disability will be measured by the WHO Disability Assessment Schedule (WHODAS 2.0)
^131,
132^. QALYs will be derived through transformation of the WHODAS 2.0 12-item scores. A probabilistic Markov decision analytic model will be built in to estimate the expected cost per outcome and the costs per QALY of SCALA from a societal perspective, based on established economic evaluation state-transition modelling guidelines
^133,
134^. Costs and effects will be modelled for five years and life time. Probabilistic sensitivity analyses will be executed.

All relevant data required for testing the scale-up will be transferred to the institution leading the evaluation work (Technische Universitaet Dresden) in accordance with its research data protocols. No individual data will be published, and data will only appear in aggregate form in project publications. On publication of the results, datasets will be made available via the UK data archive service (
http://www.data-archive.ac.uk/).

